### Assessments

As part of screening for eligibility, date of birth, gender, body height and weight, data from a health questionnaire, as well as a fall risk profile and current medications, will be collected. The health questionnaire aims to identify the presence of medical conditions (e.g., cardiovascular or neurological disease, high blood pressure, osteoporosis, acute inflammatory conditions, herniated disk, hip fractures, vision deficits). The fall risk profile is based on a composite risk score defined as the “Silver Index” (SI) which is calculated using specific parameters of the hunova robot [35]. The model is presented and validated by Cella et al. [35].

To evaluate intervention effects, a comprehensive assessment strategy which includes the SI, and a mobility test will be repeated at T_0_, T_1_, T_2_, and T_3_ (see Fig. 1 and 2). In addition to these repeated assessments, participants in the study will be instructed to keep a fall diary throughout the complete study (i.e., between T_0_ and T_3_).

#### Silver Index (SI)

Inputs into the SI are age, number of falls in the last 12 months, and the outcomes of following 8 tests for gait, balance, and rising from a chair (for detailed test procedures, and the calculation of the SI, see [35]:

Gait:
1. a 6-m walk test is used for determining gait speed;

Balance control is tested while the participant is standing on a force platform (foot platform) under the following conditions:2. quiet standing with eyes open on static foot platform (30 s);3. quiet standing with eyes closed on static foot platform (30 s);4. standing with eyes open on an unstable foot platform (responding to the participant’s postural oscillations; 30 s);5. standing with eyes open while the foot platform is moving along a default trajectory (30 s);6. reactive balance: standing with eyes open while the foot platform implements specific perturbations (with impulses of 6 degrees in random directions and in random order;7. limits of stability test: the person is instructed to move his/her body’s centre of mass as far as possible in anterior–posterior and medio-lateral directions without needing to step to maintain balance;

Muscle function (lower extremities):8. the Five Times Sit to Stand Test (FTSST) is used as a functional test for lower extremity muscle function.

Based on these tests, the SI indicating fall risk was calculated [35]. SI ranges between 0 and 100%, a score higher than 40% is considered to indicate an increased fall risk and is used as inclusion criteria for participation in this study. In addition to the overall SI, the hunova robot compares the results of seven dimensions (static balance, dynamic balance, reactive balance, limits of stability, gait speed, sensory integration, and sit to stand) to a reference sample of the same age. Based on this comparison, each dimension is defined as normal (on average) meaning no deficit or having a performance below average resulting in a yellow (poor performance), orange (very poor performance), or red deficit (very very poor performance) for this dimension. The dimensions (and deficits) are visualised in a radar plot (see Fig. 3). These dimensions and deficits are relevant for the planning of the training sessions within the intervention (see ‘intervention’).

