This paper describes a study protocol that aims to evaluate the effects of a complex fall prevention intervention on fall incidence and fall risk in older persons with an increased fall risk. The intervention comprises two consecutive components; a technology-supported exercise programme followed by a home-based exercise programme. Based on a randomised controlled design, the study will evaluate the hypotheses that the intervention reduces fall incidence (primary outcome) and fall risk (secondary outcome).

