**Fig. 1 Fig1:**
[figure not shown]
SPIRIT-Figure: Schedule of enrolment, interventions, and assessments (CTR = control group; HBEP = home-based exercise programme; INT = intervention group; TSEP = technology-supported exercise programme; X = relevant for INT and CTR; +  = only relevant for INT)

For the intervention group, T_0_ is a baseline assessment; T_1_ an assessment after finishing the technology-supported part of the intervention; T_2_ an assessment after finishing the home-based exercise programme; and T_3_ a final follow-up assessment 12 months after T_2_. In total, the training period of the intervention group comprises 2*24 units (48 sessions in total) with a training frequency of two planned training sessions of 30 min each per week. The intervention period of the technology-supported exercise programme is individually dependent on the time progress of the completed 24 sessions. Given the defined training frequency of two training sessions per week, the technology-supported exercise programme has a minimum intervention period of 12 weeks. If individual training sessions are cancelled, the intervention period may be extended, however, it is limited to a maximum of 16 weeks. Identical to the intervention period of the technology-supported exercise programme, the period of the home-based programme is then determined individually for each participant. Participants in the control group receive all four measurements. Participants in the control group are not offered any actions; they are instructed to maintain their activities as usual. The time periods between the T_0_, T_1_ and T_2_ measurements are defined as 16 weeks for the control group. Both groups end at T_3_ with a final follow-up assessment 12 months after T_2_. Figure 2 shows the detailed timeline for study participants. Participants in the control group will have the opportunity to participate in an optimized training programme using the hunova robot after the end of the study.

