
### Randomisation procedures

An equal number of participants in the intervention and control group will be determined for each study centre. For this purpose, all eligible participants draw a lot with either INT or CTR after the baseline assessment. The number of lots for INT and CTR is equal and limited. Drawn lots are not returned to the lottery pot until all lots have been drawn. The examiners of the centres have no influence on the allocation to the groups, a change between groups is not possible.

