#### Planned statistical evaluation of outcomes

An analysis of primary outcomes (i.e., number of falls and number of persons who have fallen) will be based on binomial regression analyses with demographic variables, physical activity, and health parameters as covariates. Analyses of secondary outcomes (SI and TUG) will be based on 2 × 4 ANOVA / ANCOVA with groups (INT/CTR) and time of assessment (T_0_, T_1_, T_2_ and T_3_) as factors, and will consider demographic variables, physical activity, and health parameters as co-variates. Significant main or interaction effects will be investigated further using Bonferroni post-hoc-tests. The significance level is set to *p* < 0.05.

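### The Silver Index contains the past-12-month fall count, so as a repeated outcome it can carry pre-randomisation falls at T1 and T2 and partly restate the primary outcome at T3

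*Protocol article*

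**What the plan says.** The Background sets two hypotheses, namely that "the intervention reduces fall incidence (primary outcome) and fall risk (secondary outcome"). The Silver Index section gives the composition of the score: "Inputs into the SI are age, number of falls in the last 12 months", together with the results of eight tests of gait, balance and rising from a chair. Under Assessments, the strategy for evaluating the intervention is one "which includes the SI, and a mobility test will be repeated at T_0_, T_1_, T_2_, and T_3". The statistical section then states: "Analyses of secondary outcomes (SI and TUG) will be based on 2 × 4 ANOVA / ANCOVA", with group and the four assessment times as factors.

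Randomisation follows T0: "all eligible participants draw a lot with either INT or CTR after the baseline assessment". Under Study design, "the technology-supported exercise programme has a minimum intervention period of 12 weeks" and may be extended to 16. The home-based block is set individually in the same way. Controls have fixed 16-week intervals, and T3 comes 12 months after T2 in both groups. The fall diary, which supplies the primary outcome, runs from T0 to T3.

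The Abstract, by contrast, describes the score as built from test results measured with the robot. A later sentence in the Silver Index section likewise says that it was calculated from the tests. Neither mentions fall history or age.

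**The concern.** A composite suited to classifying people at entry is not automatically a clean measure of response. One SI input is a 12-month count of the event that forms the primary outcome. At the early visits, a refreshed count still holds falls from before randomisation, which no intervention could have prevented. At the last visit it holds falls that the primary analysis has already counted.

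What is at stake is interpretation. The Discussion expects the first benefit on risk factors after the 24 robot sessions, that is at T1, where a refreshed falls item responds least. At T3 a lower SI in the intervention group could come from fewer falls, from better balance and strength, or from both. A reader relying on the Abstract would take it as device-measured performance, and might count it as a second, separate confirmation of the falls result.

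**Working it through.** **Inputs**
- Block length in the intervention group: 12 to 16 weeks, twice (Study design).
- Block length in controls: 16 weeks, twice (Study design).
- T2 to T3: 12 months, taken as 52 weeks (Study design).
- SI falls look-back: 12 months, taken as 52 weeks (Silver Index section).
- Primary-outcome period: T0 to T3 (Fall diary section).
- Planned fall reduction: 23% (sample-size section), used only for illustration.

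**Check of the timeline.** Two blocks give 2 × 12 = 24 to 2 × 16 = 32 weeks, which matches the 24–32 weeks in the Abstract. T0 to T3 is therefore 24 + 52 = 76 to 32 + 52 = 84 weeks.

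**Share of the look-back before randomisation**, if the item is refreshed: (52 − weeks since T0) / 52, not below zero.

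| Visit | 12-week blocks (fastest intervention) | 16-week blocks (all controls, slowest intervention) |
|---|---|---|
| T1 | 40/52 = 77% | 36/52 = 69% |
| T2 | 28/52 = 54% | 20/52 = 38% |
| T3 | 0% | 0% |

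The remaining 23–31% at T1 and 46–62% at T2 lies inside the primary-outcome period, so some overlap with the primary outcome exists there too.

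**Difference in timing between arms.** At T1, 16 − 12 = up to 4 weeks; at T2, 32 − 24 = up to 8 weeks. The fastest intervention participants thus have about 8 percentage points more pre-randomisation window than controls at T1 (77% against 69%) and about 15 at T2 (53.8% against 38.5%).

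**Overlap at T3.** The look-back is T2–T3, wholly inside the primary-outcome period. It makes up 52/84 = 62% to 52/76 = 68% of that period.

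**Illustration for the falls item alone.** Assume a constant fall rate and a 23% reduction from T0 onwards. The expected ratio of 12-month counts is 1 − 0.23 × post-randomisation share:
- T1: 1 − 0.23 × 12/52 = 0.95 to 1 − 0.23 × 16/52 = 0.93.
- T2: 1 − 0.23 × 24/52 = 0.89 to 1 − 0.23 × 32/52 = 0.86.
- T3: 0.77.

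These ratios concern one input, not the SI. Converting them to SI points needs the weights, which the article leaves to a cited source.

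**If the T0 value is carried forward instead,** the item is a constant for each participant. The T3 overlap and the timing difference between arms then both disappear.

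**The case against.** The strongest reply has five parts.

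1. **Refreshing is not stated.** No section says that the falls item is re-entered at each visit, and the calculation is referred to a cited source. Nor does any section say that the diary feeds the SI. This stands, and the point is therefore conditional.
2. **Window overlap is not harm.** Falls is one of ten listed inputs (age, falls, eight tests), and its weight could be negligible or dominant. This stands: no size in SI points can be given.
3. **Randomisation protects the comparison.** Falls before T0 are balanced in expectation, so they mainly dilute an effect and do not create one. This stands for visits at equal times after T0. It is weaker at T1 and T2, where the arms' visit times can differ. Age rises almost equally in both arms over 76–84 weeks and largely cancels in the group comparison.
4. **A fall-risk score naturally includes recent falls,** and the article nowhere claims that SI independently confirms the falls result. This is fair, but the Abstract does describe the score as a product of the tests.
5. **Other measures exist.** TUG is a secondary outcome at every visit, and the seven SI dimensions do not list fall history as an input. This confines the problem to the overall SI, although the statistical section does not name the dimensions as outcomes.

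A reader might infer that SI at T3 simply counts the primary outcome again, that the SI analysis is biased towards a false benefit, or that the standard SI should be reduced to a descriptive measure. The documents support none of these. The T3 window covers only part of the primary period, eight performance tests also enter the score, and the article describes the SI as validated in its standard form.

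**Conclusion.** The point holds as a conditional problem of interpretation. On the reading that the falls item is refreshed, most of its window at T1 (69–77%) and a substantial part at T2 (38–54%) predates randomisation, and its T3 window coincides with 62–68% of the primary-outcome period. An SI difference at T3 is then partly a restatement of the falls result, and an SI difference at T1 is muted to the extent that the falls item carries weight. The mix of old and new falls may differ by arm at T1 and T2; its effect on the SI cannot be determined from the article.

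The conclusion rests on three things: refreshing at each visit (not stated), the visit timings under Study design, and a weight for the falls item that is not trivial (unknown). Age drift is minor. The planned analysis of the SI is not invalid, but by itself it cannot separate a gain in performance from a change in fall counts.

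**What to change.** - Keep the standard SI as the stated secondary outcome, and leave its use for eligibility unchanged.
- State whether the falls item is updated at T1, T2 and T3 or carried forward from T0 and, if updated, from what source.
- Pre-specify a companion analysis of the SI at T1–T3 with the falls item held at its T0 value. If the formula cannot be rerun, analyse the seven test-based dimensions instead.
- Base any claim of improved performance-related fall risk on that companion analysis and TUG.
- Do not present SI at T3 as independent support for the primary outcome, and align the Abstract's description of the score with its listed inputs.

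The cost is a recalculation, with no new data collection. It assumes that the raw inputs are stored and that the device partner's formula can be rerun, neither of which the article documents; the dimensions are the fallback. The downside is small: the fixed-history SI is not the validated published form, so both versions are reported. If the item turns out to be carried forward, the standard SI already is the fixed-history version, and a sentence saying so is enough.

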**Fig. 3 Fig3:**
[figure not shown]
Radar plot as a result of the SI (Silver Index) assessment. The seven SI dimensions are displayed regarding the performance of the participants (green = normal (on average) meaning no deficit; yellow = poor performance; orange = very poor performance; red deficit = very very poor performance)

#### Mobility test

In addition to the aforementioned tests, the Timed-up-and-go test (TUG) [40] is administered during all planned assessments (T_0_, T_1_, T_2,_ and T_3_) for all included participants.

#### Fall diary

To assess the number of falls, participants are instructed to keep a diary throughout the complete study (i.e., between T_0_ and T_3_). In the context of this study, a fall is defined conform Lamb and colleagues [41] “a fall is an unexpected event in which the participant comes to rest on the ground, floor, or lower level”. In the fall diary, the participant indicates for each day whether one or more of following events [5] occurred; a ‘trip or slip’, a ‘fall without injuries’, or an ‘injurious fall’. In case of a fall, details of the fall are documented in a fall anamnesis questionnaire. After inclusion in the study, participants receive sheets for every month of their study participation. Sheets for completed months are collected every time the participants visit the study centres for assessments.

#### Questionnaires

To evaluate aspects of the intervention, several questionnaires will be administered at T_1_ (after finalising the first part of the intervention) or T_2_ (after finalising the home-based programme), and an exercise diary will be kept:• The general feedback to the technology-supported exercise programme and the general feedback to the home-based exercise programme are assessed based on custom self-developed questionnaires that aim to assess feasibility;• The Usefulness, Satisfaction and Ease of Use (USE) questionnaire, a validated and reliable instrument [42], is used to assess user satisfaction with the technology-supported exercise programme and the home-based exercise programme;• The Task Load Index (TLX), a validated and reliable questionnaire [43], is used to assess subjective effort during the technology-supported exercise programme and the home-based exercise programme;• The User Experience Questionnaire (UEQ) [44] is used to evaluate both parts of the intervention;• Based on a customised questionnaire, overall feedback to the study will be collected to assess the subjective evaluation of participating in the study’s intervention.• An ‘Exercise diary’ is used to evaluate the home-based exercise programme and subjective effort.

Lastly, as additional background information, overall health status and physical activity will be monitored throughout the complete intervention (i.e., between T_0_ and T_3_). Each month, physical activity will be assessed based on the German PAQ-50 + [45], and to assess health status, the EQ-5D-5L [46] will be used at T_0_, T_1_, T_2_ and T_3_.

### Intervention

#### Technology-supported exercise programme (TSEP)

The first intervention period refers to the technology-supported exercise programme (TSEP) using the hunova robot (Movendo Technology, Genoa, Italy). The hunova robot is a programmable robotic medical device that consists of two electromechanical platforms with two degrees of freedom, one at foot level (foot platform) and one at seat level (seat). Both platforms include two motorized axes. The platforms are rigidly connected to the robot movement axes by means of a torque and force sensor (6-axis sensor). The system allows two degrees of freedom of mobility (forwards-backwards = anterior-posterior and left-right = medio-lateral). The hunova robot can operate in static, active, passive, and assistive modes. Further details can be found in additional file 1. The hunova robot operates in conjunction with a wireless sensor (Inertial Movement Unit - IMU) located on the participant’s torso, to monitor torso motion. All exercises are accompanied by graphical and audio applications (providing biofeedback) run by the remote computer, with which the participant interacts to complete the exercises.

The participants are supervised in a 1:1 situation by a sport or physio-therapist for about 30 min per training session. By performing various functional, balance, and strength exercises on the hunova robot, the participants train within their individual deficit areas of balance and muscle strength while receiving visual feedback via a monitor.

The design of the TSEP training is planned and carried out on three levels. The first level is represented by the training areas, the second level is the type of activity and the third is the difficulty of each activity. The TSEP is the result of the combination of the three layers and the detailed description is provided in the following paragraphs. At first, there is the training layer (level 1), based on the seven subsections of the SI supplemented by a maintenance area, which consists of exercises that train the seven functional areas assessed. These eight training areas are named static balance, dynamic balance, sensory integration, reactive balance, gait speed, limits of stability, sit to stand and maintenance. For each dimension, specific exercises are possible with the hunova robot. A detailed description of all exercises implemented within the TSEP using the hunova robot is presented in Table 1.

**Table 1 Tab1:** Exercise list and descriptions (COP = centre of pressure)

Training area (level 1)	Task description	Position	Mode	Difficulty regulation (level 3)
Static balance	Participant / exercising person must maintain balance while shifting her/his COP through whole body movements	Standing bipodal or standing with one leg on foot platform, one behind	Static foot platform	- load on one leg - hands/torso reaching - inclined plane - dual task exercises - squats - leg raises
Dynamic balance	Participant / exercising person must maintain balance while the foot platform simulates changing terrain and moves in predefined directions/patterns	Standing bipodal or standing with one leg on foot platform, one behind	Active foot platform	- load on one leg - variation in movement planes - higher amplitude of motion - hands reaching - dual task exercises
Sensory integration (dynamic balance + visual integration)	Participant / exercising person must maintain balance on various simulated surfaces using visual-motor or proprioceptive integration	Standing bipodal or sitting	Static, active, passive foot platform, active, passive seat	- eyes closed - reaching - unstable surface - dual task exercises
Reactive balance	Participant / exercising person must maintain balance while the foot platform is movable and follows her/his movements	Standing bipodal or standing with one leg on foot platform, one behind	Active, passive foot platform	- load on one leg - hands/torso reaching - dual task exercises - platform gives impulses
Gait speed (dynamic balance + reactive balance)	Participant / exercising person must maintain balance while the foot platform simulates changing terrain or follows her/his movements	Standing bipodal or standing with one leg on foot platform, one behind	Active, passive foot platform	- load on one leg - platform gives impulses - torso/hands reaching - variation in movement planes
Limits of stability	Participant / exercising person must maintain balance while moving her/his COP through whole body movements following predefined patterns	Standing bipodal	Static, active, passive foot platform	- reaching (with load) - higher amplitude of motion - variation in movement planes - variation in movement patterns
Sit to stand	Participant / exercising person must maintain balance in a sitting position while moving actively or to compensate seat movement	Sitting or standing bipodal	Active, passive seat, static, active foot platform	- increasing seat movement - torso reaching - sit to stand - inclined plane - squats
Maintenance	Participant / exercising person must maintain balance while doing exercises from all training areas	Standing bipodal or standing with one leg on foot platform, one behind or sitting	Static, active, passive foot platform, static, active seat	Regulation through measures from all other training areas

To guarantee training success, basic principles of exercise / training science were considered within the training programme. To progressively increase the load and difficulty, level 2 (activity) and level 3 (difficulty) should be used. Each training area (level 1) is further divided into three different activities, including various exercises. In each activity block, there are ten different exercises resulting in 30 exercises per training area. To progressively increase the requirements alongside the activities, the following parameters are used: number of repetitions and sets, addition of dual task exercises, and reduction of the base of support. On level 3, three different difficulty levels can be used to adjust the load (and difficulty) during the exercises individually according to the number and characteristics of the deficits of the participants / exercising persons. At difficulty level “easy (E)”, each exercise has a movement duration of 30 s, and 3 sets should be performed. In the “medium (M)” difficulty level, each exercise has a movement duration of 45 s, and 2 sets should be performed, ending with “difficult (D)” with 60 s and one set. A total number of exercises of 30 in E, 20 in M, and 15 (7/8 in 2 sets) in D are possible. With this design, a net training time of 15 min should be realised, resulting in a session duration of 30 min per session. In the section of strengthening exercises, the hunova robot automatically gives instructions about movement duration, rest between repetitions and sets. For the sit to stand exercises, the therapists should control for 6 repetitions of the sit to stand exercise during difficulty level E, 8 repetitions for difficulty level M and 2 sets with 6 repetitions for difficulty level D (15 s rest between sets). Within the sit to stand movements, 2 s for concentric, 1 s isometric and 2 s for eccentric movement should be realised.

For the detailed planning and implementation of level 3 (difficulty), the number, the dimensions, and the characteristics (yellow, orange, red) of the deficits in the seven dimensions during the SI measurements must be considered (see additional file 2). In each training session (of the 24 sessions in total), one dimension is focused. Within the total training period, the two worst dimensions (depending on the SI results) are included in the exercise schedule. For standardisation purposes and for better comparability between persons, there is a fixed training progression. For this purpose, a manual was created for the sport and physio-therapists that contains every potential case that can occur within the SI measurements. It also covers the next steps for training planning and implementation. All details about this design are presented in additional file 3. If the planned training in the TSEP is too difficult for a participant, the (starting) difficulty level can be lowered by the therapists, the progression of training difficulty remains the same for these participants.

